### Statistical analysis

2.8

Efficacy will be assessed in the full analysis set (FAS) and the per-protocol (PP) set. The FAS will include all subjects who meet the inclusion/exclusion criteria, provide voluntary informed consent to participate in the study, receive at least 1 dose of the investigational product after randomization, have FMA assessment, that is, the primary efficacy endpoint, at screening, and at least once at weeks 4, 8, or 12 during the follow-up period. The PP set will include all FAS subjects who do not have any major violations such as major protocol violations (excluding minor violations) and have a primary efficacy assessment per protocol. Subjects with an overall medication compliance of <70% will be excluded from the PP set. Safety will be assessed in the safety set, which will comprise of all subjects who receive at least 1 dose of the investigational product after randomization.

The primary efficacy endpoint will be analyzed both in the FAS and the PP sets. The final conclusions of the study will be made based on the FAS results, in principle. Mean, SD, median, and range (minimum, maximum) of FMA motor score before dosing and 12 weeks after dosing, as well as score change between the 2 time points, will be presented for the high- and low-dose HT047, and the placebo groups. To assess intergroup differences in the primary endpoint, that is, FMA change, analysis of covariance, with baseline FMA as a covariate, and Tukey multiple comparison test will be carried out. Dunnett multiple comparison, which would consider the placebo group as a comparator group, will not be used because this phase 2 study aims to evaluate adequate dosage and therefore, will compare the HT047 high-dose group with the HT047 low-dose group.

The secondary efficacy and exploratory endpoints will be also analyzed both in the FAS and the PP set, with the final conclusions to be made based on the PP set results. For each secondary efficacy and exploratory endpoint, mean, SD, median, and range (minimum, maximum) will be presented by the group for continuous data, whereas frequency and percentage will be provided by the group for categorical data. For the following secondary efficacy endpoints, generalized estimating equation analysis will be conducted for overall data or by subgroup, according to the relevant definition. For generalized estimating equation analysis, the following intergroup differences in FMA score change at each time point will be assessed by performing a contrast analysis, while a trend analysis will be conducted to characterize the trend in FMA change between time points by group: intergroup comparison of change in FMA motor score at weeks 4 and 8 from the baseline; intergroup comparison of FMA motor score change at weeks 4, 8, and 12 from the baseline according to the timing of treatment initiation after the onset of stroke (either within 1 week or 1–2 weeks), and according to the presence of prognostic risk factors (hypertension, diabetes, dyslipidemia, etc); intergroup comparison of change in K-NIHSS and K-mRS scores at weeks 4 and 12 from the baseline; and intergroup comparison of change in K-MBI score at weeks 4 and 12 from the baseline. For the following secondary efficacy endpoints, a Chi-squared test will be conducted, and if there is an intergroup difference in proportion, a Hochberg test will be carried out to compare the HT047 high-dose, HT047 low-dose, and placebo groups to control for multiplicity issues: intergroup comparison of the proportion of subjects with K-NIHSS score 0 to 2 at week 12; intergroup comparison of the proportion of subjects with K-mRS score 0 at week 12; intergroup comparison of the proportion of subjects with K-mRS score ≤1 at week 12; and intergroup comparison of the proportion of subjects with K-mRS score ≤2 at week 12. To assess intergroup difference in the exploratory endpoint, that is, change in MoCA-K score at week 12 from the baseline, analysis of covariance and Tukey multiple comparison test will be carried out.

A comprehensive statistical analysis plan will be finalized prior to database locking. Details of statistical analyses that are not presented in the protocol will be described in the statistical analysis plan. All statistical analyses will be performed at a 2-sided significance level of 10%. To handle the missing data, the last observation carried forward method will be used for FMA motor score, the primary outcome variable. If FMA motor score is measured only at screening, substitution for missing data will not be performed. Similarly, for the other outcome variables, missing data will not be substituted and included in the statistical analysis. Interim analysis will not be performed.

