### Study setting

2.1

The participants will be recruited from eight institutes in the Republic of Korea, including the Departments of Neurology at Kyung Hee University Hospital (Seoul), Kyung Hee University Hospital at Gangdong (Seoul), Hanyang University Hospital (Seoul), Hanyang University Guri Hospital (Gyeonggi-do), Hanyang University Myongji Hospital (Gyeonggi-do), Gachon University Gil Medical Center (Incheon), Hallym University Dongtan Sacred Heart Hospital (Gyeonggi-do), and Chosun University Hospital (Gwangju). Regular investigators’ meetings will be held to encourage enrollment and regular newsletters will be sent until the required sample size is reached. The 1st patient was enrolled in August 4, 2016.

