### Interventions

2.4

The HT047 will be produced by Bioland Co, Ltd, a bulk Good Manufacturing Practice-certified manufacturer (Osong, Chungcheongbuk-do, Republic of Korea). The dried roots of *P lobata* and *S baicalensis* will be mixed together in an 8.0:1.1 weight ratio and then be extracted twice with 30% ethanol in distilled water for 3 hours at 70°C. The liquid extract will be filtered, concentrated under 60°C, and vacuum dried to yield the extract, HT047. The study drug (a tablet containing 250 mg of HT047) and a placebo, identical in appearance to the study drug, will be provided by Kolmar Korea Inc (Sejong-si, Republic of Korea).

Participants will receive either the investigational product (HT047) or placebo 3 times a day for 12 weeks, starting from the morning after the baseline visit. Three tablets will be administered per dose as follows: 3 HT047 tablets for high-dose group (2250 mg/d), 2 HT047 tablets, and 1 placebo tablet for low-dose group (1500 mg), and three placebo tablets for placebo group. A one-month supply of the investigational products will be given to the subjects at baseline and weeks 4 and 8. At each visit, subjects will be asked to return the remaining investigational products for calculating their compliance and will be encouraged to adhere to the prescribed dosage regimen.

Physiotherapy sessions will be freely prescribed by the patient's attending physician, neurologist, or rehabilitation physician, according to medical opinion and subjects’ requests. Subjects will be prohibited from concomitant use of any medications which can induce hepatotoxicity, such as propylthiouracil, ketoconazole, isoniazid, valproate, and phenytoin; any medications containing *P lobata*, *S baicalensis*, or their major components (puerarin and baicalin, respectively); selective serotonin reuptake inhibitors; amphetamine; cholinesterase inhibitors, such as donepezil, rivastigmine, and galantamine; memantine; nootropics, such as choline alfoscerate, acetyl-l-carnitine, oxiracetam, and *Ginkgo biloba.*

The allocated intervention will be discontinued if a participant or a participant's legal representative wishes to discontinue study participation or if the investigator decides to discontinue due to medical or administrative reasons (adverse events, continuous protocol violations, etc).

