### Randomization and blinding

2.5

Eligible participants will be randomly assigned to one of the following 3 groups in a 1:1:1 ratio: high-dose (750 mg 3 times a day), low-dose (500 mg 3 times a day), and placebo groups. An independent statistician will generate a list of random numbers using a centralized stratified block randomization method. Randomization will be stratified according to the hospital, so that all hospitals have a 1:1:1 ratio. The study drug and placebo will be sealed in sequentially numbered identical bottles according to the allocation sequence. Each participant will be assigned an order number and will receive the investigational product or placebo in the corresponding prepacked bottles. Participants and all research personnel will be blinded to the assignment. The randomization code will be kept secure by an independent statistician and can only be broken in the case of an emergency. If a code break occurs, the investigator will report the reason and procedures and the administration of investigational drug will be discontinued.

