### Outcome measures and endpoints

2.6

The Korean version of the FMA motor score will be used to measure the primary endpoint.^[19]^ The motor domain of FMA ranges from a score of 0 (flaccid hemiplegia) to 100 (normal movement), with 66 points for the upper limb and 34 points for the lower limb. An educated physiotherapist will perform all motor assessments at baseline and weeks 4, 8, and 12. The K-NIHSS and Korean versions of the modified Rankin scale (K-mRS), the modified Barthel index (K-mBI), and the montreal cognitive assessment (MoCA-K) will be used at baseline and weeks 4 and 12.

The primary efficacy endpoint is the change in FMA motor score at week 12 from the baseline. The secondary efficacy endpoints are: the change in FMA motor score at weeks 4 and 8 from the baseline; the change in FMA motor score at weeks 4, 8, and 12 from baseline according to the timing of treatment initiation after the onset of stroke (either within 1 week or 1–2 weeks) or according to the presence of prognostic risk factors (hypertension, diabetes, dyslipidemia, etc); the change in K-NIHSS and K-mRS scores at weeks 4 and 12 from the baseline; the proportion of subjects with a K-NIHSS score of 0 to 2 at week 12; the proportion of subjects with a K-mRS score of 0, ≤1, and ≤2 at week 12; and the change in K-MBI score at weeks 4 and 12 from the baseline. Exploratory endpoint is the change in MoCA-K score at week 12 from baseline.

Safety endpoints are the adverse events, significant changes in vital signs and physical examination; and abnormal laboratory tests, electrocardiogram, and chest radiography results. Laboratory tests will include hematology, electrolyte, blood chemistry, lipid battery, blood coagulation, and urinalysis.

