### Sample size

2.7

The primary endpoint of the study is the change in FMA motor score at baseline from that after 12 weeks. A sample size of 22 in each group will be sufficient to detect a clinically important difference of 14.5 points on the FMA score, assuming a standard deviation (SD) of 19.2. This estimate is based on the findings of the fluoxetine in motor recovery of patients with acute ischemic stroke trial, which reported a difference of mean ± SD 90-day FMA score change between fluoxetine group (n = 57, 36.4 ± 21.3) and control group (n = 56, 21.9 ± 16.7).^[20]^

Because this HT047 trial is a phase 2 exploratory clinical trial for appropriate dose selection, we did not consider adjustment to control for type 1 errors resulting from the comparison between the 3 groups. However, in the comparison of primary efficacy outcome between the 3 groups, multiple comparisons will be performed to control for the experiment-wise error rate. We will use a Student *t* test of the difference between mean values, a power of 80%, and a significance level of 10%. With a 15% anticipated drop-out rate considered, we plan to enroll 26 patients per group (a total of 78 patients).

The formula for the sample size for comparison of 2 mean values is as follows:
 
[figure not shown]

where *Z*_*α*/2_ is the normal distribution threshold of type 1 error (*α* = 0.10/2), *Z*_1-*β*_ is the normal distribution threshold of power (1 − β = 0.8), *μ*_*T*_ is the mean change of 12-week FMA score in HT047 group (high dose or low dose), *μ*_*C*_ is the mean change of 12-week FMA motor score in control group, and σ is the standard deviation.

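### Randomisation is stratified by hospital, but the stated primary ANCOVA has no hospital term; if hospitals differ, its standard error is too large and the test conservative

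*Protocol article*

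**What the plan says.** All references are to the protocol article.

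- **Study setting:** "The participants will be recruited from eight institutes in the Republic of Korea".
- **Randomization and blinding:** the list is generated "using a centralized stratified block randomization method". "Randomization will be stratified according to the hospital, so that all hospitals have a 1:1:1 ratio". No other stratification factor is named, and no block size is given.
- **Outcome measures and endpoints:** "The primary efficacy endpoint is the change in FMA motor score at week 12 from the baseline".
- **Statistical analysis:** the primary endpoint is analysed by "analysis of covariance, with baseline FMA as a covariate", followed by Tukey comparisons. Neither the primary model nor the secondary and exploratory analyses name a hospital term, and no reason is given. The same section leaves to the SAP those details that the protocol does not present.
- **Interventions:** "Physiotherapy sessions will be freely prescribed" by the treating physicians, according to medical opinion and the subject's requests.

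**The concern.** Blocking within hospital forces the arms to be nearly equal in each hospital. Differences between hospitals in mean recovery then largely cancel out of the treatment comparison, so the true sampling variance of the estimate falls. An ANCOVA without hospital does not know this. It counts the between-hospital variance as residual noise and reports a standard error larger than the true one. Confidence intervals come out too wide, and a real effect is declared less often than the data warrant.

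Hospital differences are plausible here. Physiotherapy, which bears on motor recovery, is not standardised, and the choice of hospital as the only stratum suggests that the sponsor expected it to matter. With 22 evaluable patients per arm, avoidable loss of power deserves attention.

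**Working it through.** **1. The plan's own figure.** The Sample size section gives a "clinically important difference of 14.5 points on the FMA score, assuming a standard deviation (SD) of 19.2", 80% power and a 10% two-sided level:

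n = 2 × 19.2² × (1.645 + 0.842)² / 14.5² = 21.7, rounded up to 22 per arm; 22 / 0.85 = 25.9, rounded up to 26 per arm, 78 in total.

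The sample size reproduces, so the point does not rest on an arithmetic error. Evaluable patients: 3 × 22 = 66.

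**2. What the two models estimate.** Let h be the share of outcome variance due to hospital and r the correlation of outcome with baseline. With 22 per arm, the reported standard error of a pairwise difference is approximately:

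- without hospital: 19.2 × √(1 − r²) × √(2/22)
- with hospital: 19.2 × √(1 − r² − h) × √(2/22)

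The article gives neither h nor r. Assume r = 0.3 and h from 0 to 20%. Without hospital: 19.2 × √0.91 × 0.3015 = 5.52, whatever h is. With hospital: 5.21 at h = 10% (√0.81) and 4.88 at h = 20% (√0.71). Because allocation is blocked within hospital, the smaller figure is close to the true sampling SD under either model.

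**3. Tukey reference point.** For three groups at a 10% family-wise level and 66 − 4 = 62 degrees of freedom, the Tukey critical value on the t scale is about 2.09. Its per-pair size, P(|t| > 2.09), is about 4%. That is the benchmark for a valid pairwise test here, not 10%.

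**4. Simulation.** Assumed: 66 patients; hospital sizes 18/12/10/8/6/6/4/2; permuted blocks of 3; total SD 19.2; r = 0.3; true difference 0 or 14.5 in one active arm against placebo; 8,000 trials per cell. Each trial was analysed with and without hospital as a fixed effect (55 and 62 degrees of freedom), using the Tukey critical value.

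| Hospital share of variance (assumed) | Mean reported SE, without / with hospital | True SD of estimate, without / with | Tukey power, without / with |
|---|---|---|---|
| 0% | 5.55 / 5.60 | 5.54 / 5.59 | 69% / 68% |
| 5% | 5.54 / 5.44 | 5.54 / 5.57 | 70.5% / 71.4% |
| 10% | 5.51 / 5.28 | 5.25 / 5.26 | 70% / 73% |
| 20% | 5.46 / 4.94 | 5.00 / 4.98 | 73% / 79% |

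(Standard errors and SDs are from the runs with no true effect. Monte Carlo error is about 0.5 points on power.)

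The true SD of the estimate is practically the same with and without hospital in every row. Only the reported standard error differs. At 20%, the per-pair Tukey size without hospital is about 2.5 to 3% instead of about 4%; with hospital it returns to about 4%. Blocks of 6 give the same pattern.

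**5. Sensitivity to the test.** With a plain t test at 10% in place of Tukey (blocks of 6, randomly varying hospital sizes), the gain from adding hospital is smaller: about 0 points at 5%, 1 at 10% (81.8% to 82.7%) and 4 at 20% (82.0% to 85.7%).

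**The case against.** **The SAP may already include hospital.** The article names baseline FMA as a covariate without saying that it is the only one. Its ANCOVA for the cognitive score names no covariate at all, so it does not list model terms exhaustively. Centre terms and pooling rules are often left to the SAP, which is not shown. This stands as a limit: the article does not prove that hospital is excluded. But the primary model and its covariate are stated, and only details not presented are deferred. Read as written, the model has no hospital term. If the SAP adds one, the two texts need aligning.

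**Hospital effects may be small.** Physiotherapy depends on medical opinion and patients' requests, which can vary within a hospital as much as between hospitals. The Discussion describes offline FMA training given to researchers at the individual institutions by a specialist, and stable rater leniency largely cancels in a change score adjusted for baseline. This also stands. At a 5% share the gain is about 1 point of power, and at 0% adjustment costs about 1 point.

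**Three stronger readings are tempting and not supported.**

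- That leaving out hospital discards the benefit of stratification. It does not: balance and the precision of the estimate are retained (step 4, true SD column), and only the reported uncertainty is overstated.
- That the primary test runs at about 7% instead of 10%. That describes a plain pairwise t test at a 20% share. The planned Tukey test has a per-pair size of about 4% when valid.
- That the shortfall of Tukey power below 80% comes from the missing hospital term. It arises mainly because the trial was sized on an unadjusted t test, which is a separate matter.

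**Conclusion.** The point holds as a matter of efficiency and of matching the analysis to the design. The only stratification factor is absent from the stated primary model. If hospitals differ, the consequence is an overstated standard error and a conservative test. Neither bias nor inflated type I error follows.

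The size depends on an unknown. Over an assumed hospital share of 0 to 20%, adding hospital changes Tukey power by about -1 point at 0%, +1 at 5%, +2 to +4 at 10% and +6 to +7 at 20%. The hospital share, hospital sizes, block size and baseline correlation are all assumptions. The direction of the effect does not depend on them as long as hospitals differ, but a small share can be offset by the degrees of freedom spent. The change is worth making because the possible gain exceeds the possible loss. In a trial that describes itself as exploratory phase 2, its omission would not invalidate the result.

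**What to change.** State the primary model as ANCOVA of FMA change with treatment, baseline FMA and hospital, followed by the planned Tukey comparisons. Hospital may be a fixed effect, with a rule for pooling very small hospitals set before unblinding, or a random effect. A pooling rule is needed because 78 patients over 8 hospitals and 3 arms is 78 / 24, or about 3 per arm per hospital. Use the same term in the continuous secondary and exploratory models where numbers allow; subgroup analyses may be too sparse. The chi-squared analyses need no change on this account, and neither does the handling of missing data. If the sponsor prefers to leave hospital out, the reason should be stated.

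Cost: wording in the protocol and SAP, and up to 7 degrees of freedom (62 to 55), or about 1 point of power if hospitals do not differ. No extra patients or data are required.

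### With three groups, a step-down version of the planned Tukey test keeps all three comparisons and the 10% family-wise limit and is more powerful than single-step Tukey

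*Protocol article*

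**What the plan says.** Section 2.8 (Statistical analysis) specifies for the change in FMA motor score that "analysis of covariance, with baseline FMA as a covariate, and Tukey multiple comparison test will be carried out". It explains the choice by elimination: "Dunnett multiple comparison, which would consider the placebo group as a comparator group, will not be used", because the trial is meant to inform dosage and "will compare the HT047 high-dose group with the HT047 low-dose group". Section 2.7 (Sample size) gives the aim for the primary outcome: "multiple comparisons will be performed to control for the experiment-wise error rate". The level is set in section 2.8: "All statistical analyses will be performed at a 2-sided significance level of 10"%.

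The sample size in section 2.7 rests on an unadjusted two-group t test with 80% power at 10%, for a "clinically important difference of 14.5 points on the FMA score" and an SD of 19.2. The protocol says openly that at this stage "we did not consider adjustment to control for type 1 errors resulting from the comparison between the 3 groups". No stepwise or closed procedure is named for the primary endpoint; a Hochberg test is named only for the secondary proportions.

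**The concern.** Section 2.8 weighs only two methods: Dunnett, which drops high versus low, and Tukey, which keeps it. A third option keeps all three comparisons and the same family-wise limit, and needs no more patients.

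With three means, any two equalities imply the third. Once the hypothesis that all three are equal is false, at most one pairwise null can be true, so no further correction among the pairs is needed. Single-step Tukey still holds every pair to the critical value designed for the case where all three are equal. What is at stake is power on the primary endpoint, chiefly for showing that both doses work and for telling high from low.

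**Working it through.** **Inputs.** From section 2.7: difference 14.5, SD 19.2, 22 evaluable and 26 enrolled per group, 80% power. From section 2.8: two-sided 10%, ANCOVA with one covariate. Assumed: equal group sizes, the same SD in all arms, no variance reduction from the baseline covariate, and Tukey as single-step.

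**The plan's own figure.** n = 2(1.645 + 0.842)² × 19.2² / 14.5² = 21.68, so 22 per group. Then 22 / 0.85 = 25.9, so 26. Both reproduce. The exact two-group t test at 22 per group has power 79.4%.

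**Critical values at 22 per group.** Degrees of freedom: 66 − 3 − 1 = 62. Standard error of a difference: 19.2 × √(2/22) = 5.79. Unadjusted critical t: 1.670. Tukey: 2.957/√2 = 2.091, a nominal p of about 0.041 per pair instead of 0.10. With noncentrality 14.5/5.79 = 2.50, the noncentral t gives Tukey power of 66.1% per dose.

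**Closed procedure.** The pairwise nulls have only one intersection, the hypothesis that all three means are equal. Testing that at 10% and then each pair at 10% is therefore the full closed test. Results from 1,000,000 simulated trials per scenario, 22 per group unless stated (effects are low/high versus placebo):

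| Scenario | Quantity | Single-step Tukey | Range test first | F test first |
|---|---|---|---|---|
| 14.5/14.5 | each dose vs placebo | 66.1% | 73.6% | 74.5% |
| 14.5/14.5 | both doses shown | 51.3% | 66.1% | 67.4% |
| 14.5/14.5 | at least one dose shown | 81.0% | 81.1% | 81.6% |
| 0/14.5 | high vs placebo | 66.1% | 73.6% | 74.5% |
| 0/14.5 | high vs low | 66.1% | 73.5% | 74.4% |
| 7.25/14.5 | high vs placebo | 66.1% | 68.7% | 69.0% |
| 7.25/14.5 | low vs placebo | 20.7% | 31.6% | 32.3% |
| 7.25/14.5 | high vs low | 20.9% | 31.7% | 32.4% |
| 14.5/14.5, 26 per group | each dose vs placebo | 73.8% | 80.7% | 81.5% |

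**Family-wise error.** All three means equal: 10.0% for every method. Doses equal, both at 14.5: Tukey 4.1%, closed tests 9.6% to 9.7%. Only the high dose works: Tukey 4.0%, closed tests 9.6% to 9.7%. The extra power comes from the part of the 10% that Tukey leaves unused in these cases.

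**Does the step-down test ever lose a Tukey rejection?** With the range test first, no: the first step rejects exactly when some pair exceeds 2.091, and any such pair also exceeds 1.670. With the F test first, yes. If the low-dose mean lies midway, F = t²/2; at t = 2.091 that is 2.19, below the 10% critical value of 2.39. In the scenarios with an effect, about 0.9% (14.5/14.5) to 1.3% (7.25/14.5) of trials have a Tukey rejection that the F-first test misses.

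**The case against.** The strongest reply is that nothing in the text is wrong. Tukey controls the family-wise error, covers the three pairs and was chosen for a stated reason. That stands: this is an efficiency point, and a reader who infers that the planned analysis is invalid, or contradicts the stated error control, goes further than the document allows. An analysis plan that is not shown might also specify a stepwise form; the protocol does not say either way.

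Second, the gain is not free. If the doses are equal and effective, a false claim that they differ rises from about 4% to nearly 10%; if only the high dose works, a false claim for the low dose rises in the same way. Preferring the stricter test for dose selection is defensible. But the protocol's own limit is 10%, and the step-down test stays within it.

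Third, one might infer a uniform gain of about 7 points per dose. The table does not support that: the gain is 7.5 points for a dose with the full effect when the other dose matches it or has none, but about 2.5 points for the high dose when the low dose has half the effect. When both doses work, the chance of showing at least one is unchanged.

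Fourth, Tukey supplies matching simultaneous intervals, useful for planning phase 3. After the change, a Tukey interval may include zero beside a significant step-down test. This is a real but small cost.

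**Conclusion.** The point holds as a cheap improvement, not as an error in the protocol. For three groups, the range test followed by unadjusted pairs at 10% meets both of the protocol's stated requirements (high versus low retained, family-wise error held at 10%) and never rejects less than single-step Tukey. An overall F test as the first step also controls the error and has slightly higher average power, but it does not strictly dominate Tukey.

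Under the design assumptions at 22 per arm, power per dose rises by 7.5 points and power to show both doses by about 15 points. With effects of 7.25 and 14.5, low versus placebo and high versus low each gain about 11 points and the high dose about 2.5.

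The change should not be read as restoring the planned 80%: power per dose at 22 per arm is about 74%, and passes 80% only near 26 evaluable per arm. It narrows the gap between unadjusted sizing and adjusted analysis without closing it. The figures depend on the assumptions listed with the inputs; a useful baseline covariate would raise power for all methods.

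**What to change.** In section 2.8, keep the ANCOVA and replace the Tukey sentence with a two-step rule. Step 1: apply Tukey's range test at 10% to the largest studentised adjusted difference among the three groups. Step 2: only if it rejects, test each of the three adjusted pairwise differences at two-sided 10%. State that this is a closed procedure controlling family-wise error at 10%, and carry the same wording into the analysis plan, which the protocol says will be finalized before database lock.

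In section 2.7, state the power of this procedure at 22 and 26 per arm under more than one dose-response pattern.

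If Tukey simultaneous intervals are reported, add that they may not agree exactly with the tests. The cost is wording only: no change to patients, visits or data. What is given up is the exact match of tests and intervals, and the lower error rate that Tukey happens to have when only one pair is equal.

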### Design

1.2

This study is a phase 2, multicenter, double-blind, randomized, placebo-controlled, superiority trial with 3 parallel groups. Eligible participants will be randomly assigned to 1 of 3 groups: HT047 high- or low-dose, or placebo with a 1:1:1 allocation ratio, and will receive the investigational product for 12 weeks.

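### Secondary and exploratory conclusions rest on the per-protocol set in a superiority trial; the full analysis set should decide them, as it does the primary endpoint

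*Protocol article*

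**What the plan says.** The Design section (1.2) fixes the type of trial: "This study is a phase 2, multicenter, double-blind, randomized, placebo-controlled, superiority trial with 3 parallel groups".

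Section 2.8, Statistical analysis, sets two different rules for which population decides.

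- **Primary endpoint** (FMA motor change at week 12): analysed in both sets, and "The final conclusions of the study will be made based on the FAS results, in principle".
- **Secondary and exploratory endpoints**: both sets are used here too, but the deciding one changes: "with the final conclusions to be made based on the PP set results".

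The same section defines the sets. The FAS needs eligibility, consent, at least one dose, a screening FMA and at least one FMA at week 4, 8 or 12. The PP set keeps the FAS subjects who have no major violation and who have a primary efficacy assessment done per protocol. In addition, "Subjects with an overall medication compliance of <70% will be excluded from the PP set". No reason is given for letting the PP set decide everything except the primary endpoint.

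**The concern.** Compliance, protocol violations and completion of the primary assessment all arise after randomisation. Treatment can influence them through tolerability, and so can the course of recovery. A comparison restricted by such events is no longer protected by the allocation. For that reason the PP set is normally supportive in a superiority trial.

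Two consequences follow from the text.

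- **One scale, two populations.** Overall FMA change at week 12 is decided on the FAS. FMA change at weeks 4 and 8, and week-12 change by time to treatment or by risk factor, is decided on the PP set. The overall and subgroup results need not agree, for reasons unrelated to the drug.
- **A stated objective depends on the PP set.** Whether HT047 enhances neurologic recovery is a secondary objective (section 1.1), and the K-NIHSS, K-mRS and K-MBI endpoints bear on it. If tolerability depends on dose, exclusions could also differ between the high- and low-dose arms. Section 2.8 gives that comparison as the reason for choosing Tukey over Dunnett.

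**Working it through.** **1. The plan's own figure.** Section 2.7 gives a difference of 14.5, SD 19.2, two-sided alpha 0.10 and power 80%.

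- n = 2 × [19.2 × (1.645 + 0.842) / 14.5]² = 21.7, so 22 per group.
- 22 / 0.85 = 25.9, so 26 per group and 78 in total.

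The stated sample size reproduces. It does not depend on the point made here.

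**2. Which set decides what.**

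| Endpoint | Deciding set |
|---|---|
| FMA change, week 12, overall | FAS |
| FMA change, weeks 4 and 8 | PP |
| FMA change, weeks 4, 8 and 12, by subgroup | PP |
| K-NIHSS, K-mRS, K-MBI | PP |
| MoCA-K | PP |

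The compliance criterion is an overall one, and the primary endpoint is at week 12. A patient with a valid week-4 value can therefore apparently be removed from the week-4 conclusion by something that happens later.

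**3. Size of a possible bias (illustration).** The article gives no PP exclusion rates, so the rates and correlations below are assumptions. Suppose there is no true effect, a fraction q of an arm is excluded, and exclusion follows a latent score that correlates ρ with outcome, so that worse outcomes leave more often. The retained mean then shifts by

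ρ × σ × φ(z_q) / (1 − q), with σ = 19.2.

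- q = 0.20: 0.280 / 0.80 = 0.350
- q = 0.15: 0.274
- q = 0.10: 0.1755 / 0.90 = 0.195

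The bias in the treatment difference is the gap between arms:

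- **15% vs 15%:** 0.274 − 0.274 = 0, so no bias.
- **20% vs 10%:** 19.2 × (0.350 − 0.195) = 2.98, times ρ. This is 0.9 points at ρ = 0.3 and 2.1 at ρ = 0.7.

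**4. Simulation.** 26 per arm, one unadjusted pairwise t test at two-sided 10%, 5,000 runs per setting, ρ from 0.3 to 0.7. Exclusions are whole patients, so 20% vs 10% becomes 5 vs 3 of 26 (19.2% vs 11.5%).

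| Excluded, active vs placebo | Spurious difference (points) | Type I error |
|---|---|---|
| 15% vs 15% | about 0 | 10.3% to 13.2% |
| 20% vs 10% | 0.6 to 1.7 | 10.5% to 13.5% |
| 30% vs 10% | 1.7 to 3.7 | 11% to 20% |

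At 5 vs 3 of 26 the formula gives 19.2 × (0.338 − 0.220) = 2.27, times ρ. That is 0.7 to 1.6 points, in agreement with the simulation.

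The type I column needs care. Its Monte Carlo standard error is √(0.1 × 0.9 / 5000) = 0.4 percentage points. The equal-exclusion row also rises above 10% although its difference is unbiased. Removing a fixed number of low-ranked patients makes the retained values look less variable than the mean really is. The rise at 20% vs 10% is therefore not due to unequal exclusion alone. The spurious difference is the cleaner measure.

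**The case against.** **The consequence is limited.** This stands. The primary conclusion already rests on the FAS, FAS results will exist for every secondary endpoint, the rule is pre-specified, and section 2.7 describes the trial as exploratory. The fault lies in which of two planned results is named as deciding for supportive endpoints.

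**A reader might infer a definite inflation of the HT047 effect.** Removing 15% of an active arm who do 10 points worse than the arm average raises that arm's mean by 0.15 / 0.85 × 10 = 1.8 points. Removing exactly the worst 15% raises it by 0.27 SD, or 0.274 × 19.2 = 5.3 points. Removing four non-responders turns 11/26 (42%) into 11/22 (50%). The arithmetic is right, but the documents do not support the inference:

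- These are shifts within one arm. They bias the difference only if the other arms have no comparable exclusion.
- The 15% in section 2.7 is anticipated drop-out, not PP exclusion. The 11 responders are hypothetical.
- Outcomes other than FMA are not imputed, so a patient who drops out before week 12 would apparently be missing from the FAS result for that visit as well. At week 12 only patients with outcome data who fail a PP criterion separate the two sets, and their number is unknown.

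**The direction is not given.** This also stands. Patients who recover well might stop tablets too. Section 2.4 prohibits SSRIs and nootropics, but nothing shown says that their use counts as a major violation.

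**The FAS is not the full randomised set.** True. It too requires a dose and a post-baseline FMA.

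None of this is a reason to let the more selected of the two sets decide.

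**Conclusion.** The point holds as a should-fix. In a superiority trial the article lets a set defined by post-randomisation compliance and violations decide every secondary and exploratory endpoint, without a reason, while the FAS decides the primary endpoint.

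Bias arises only if exclusions differ between arms and relate to outcome. Under the assumed 20% vs 10%, it is about 0.6 to 1.7 FMA points in whole patients, or up to 2.1 from the formula. The latter is about 14% of the 14.5-point planning difference (2.1 / 14.5). With equal exclusion by one mechanism it is essentially nil. Size and direction in this trial cannot be derived from the documents.

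A reader might also infer that the two sentences on final conclusions contradict each other outright, or that the trial's main result is compromised. The FAS sentence stands with the primary endpoint and can be read as limited to it, so a contradiction is not established. The primary analysis is untouched.

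**What to change.** In section 2.8, and in the analysis plan, change the clause on secondary and exploratory endpoints so that final conclusions rest on the FAS, and add that PP results are supportive. This matches the rule for the primary endpoint. Make the change before unblinding, because a later switch of the deciding set would look driven by results.

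The cost is one sentence. No new data or analyses are needed, and the sample size does not change. Estimates may be slightly diluted by non-compliance. Selection is reduced, not removed, because the FAS still requires a dose and a post-baseline FMA and the outcomes other than FMA are not imputed.
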